##### Metabolic parameters

Changes in metabolic determinants, in particular changes in body mass, visceral fat mass (DEXA), insulin sensitivity (HOMA-IR), and adiponectin will be analysed via comparison of Baseline and follow-up data and visually checking the outcome measures moved in the expected direction for each allocation group. Paired statistical analysis (Chi-square and t-tests) may be conducted between intervention and control groups, if the sample size warrants.

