#### Sample size

This Phase 1b safety and dose-ranging study will include 45 participants with 15 to be infected with 20 x L3, 15 to be infected with 40 x L3, and 15 in the placebo control group. In the absence of other effect size data from human trials upon which to base a power calculation, and as a change in HOMA-IR from Baseline is a primary metabolic outcome of this study, we have adapted the SUGARSPIN HOMA-IR result [29] and assume an effect size of 1.06 over 2 years. A total of 15 participants in each group reflects 80% power to detect an effect size of 1.06 using the T-statistic and 1.023 using Z-statistic. The aim to recruit 54 participants allows for a potential drop-out rate of 20%.

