##### Impact of helminth infection on immune status

Serum samples collected at each scheduled visit will be batch-analysed using a custom-panel of 17 cytokines (IFNγ, IL-1β, IL-12p70, IL-2, IL-4, IL-6, TNF, IL-10, IL-17A, IL-12p40, IL-5, IL-13, IL-15, IL-18, IL-33, MCP-1, MIP-1α) for circulating inflammatory biomarkers associated with metabolic disease using cytometric bead array. Mean cytokine levels in placebo and hookworm groups will be compared by general linear models. Peripheral blood mononuclear cells will be processed at scheduled visits and analysed using flow cytometry for expression of markers of cell phenotype (CD3, CD19, CD4, CD8), activation (CD27, CD45RA, CD45RO, CD69) and function (CD25, CRTH2, CTLA4, FOXP3, IL-2, IL-4, IL-5, IL-10, IL-17A, IFNγ and TNF).

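### Metabolic outcomes get only a within-arm comparison with a visual check and an optional paired test between independent arms, which does not match the unpaired test behind the sample size

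*Protocol article*

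**What the plan says.** The Metabolic parameters section sets out two steps for the metabolic determinants.

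- The committed step is "comparison of Baseline and follow-up data and visually checking the outcome measures moved in the expected direction for each allocation group".
- The optional step is "Paired statistical analysis (Chi-square and t-tests) may be conducted between intervention and control groups, if the sample size warrants".

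The Sample size section treats one of these determinants as the basis for the trial's size. It states that "a change in HOMA-IR from Baseline is a primary metabolic outcome of this study", and that "A total of 15 participants in each group reflects 80% power to detect an effect size of 1.06 using the T-statistic and 1.023 using Z-statistic".

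Table 1 and the Design section describe three block-randomised parallel groups of 15 and mention no matching. The Outcomes section lists both longitudinal and between-cohort changes in metabolic parameters as secondary outcomes. The Aims section calls this part of the work exploratory.

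**The concern.** The two steps do not add up to a defined treatment comparison for the outcome on which the trial was sized.

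- **Paired between groups.** The intervention and control arms contain different people. A paired t-test across them needs a pairing that the design does not supply, and a paired chi-square (McNemar) has no meaning without matched pairs.
- **Paired within an arm.** If the word refers to Baseline against follow-up, the test does not compare arms. A time trend over two years would be credited to the infection. So would regression to the mean, because one route into the trial is a HOMA-IR above 2.12 (Inclusion criteria). How large that regression would be cannot be worked out from the article: there is a second entry route, and the baseline visit is separate from screening.
- **Conditional testing.** Whether to test is left to a later view of the sample size, although that size is already fixed and justified for this outcome.

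At stake is the estimate of each dose's effect on HOMA-IR, which bears on one of the trial's four hypotheses.

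**Working it through.** **Inputs.** The Sample size section gives 15 per arm, 80% power, and effect sizes of 1.06 (t) and 1.023 (z). No alpha or sidedness is stated there, so two-sided 0.05 is assumed. No standard deviation is given. The baseline–follow-up correlation r is not in the article, so it is varied from 0.5 to 0.9.

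**Step 1: reproduce the plan's figure.** For two independent samples of n per arm and standardised difference d, the noncentrality is d√(n/2) with 2n − 2 degrees of freedom.

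- t-test: 1.06 × √7.5 = 2.903, 28 df, critical value 2.048. Power is 0.800.
- z-test: the smallest detectable d is (1.960 + 0.842) × √(2/15) = 1.023. Power is 0.800.
- One-sided 0.05 gives a t-test power of 0.882, which does not match.

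Both stated figures therefore come from an unpaired between-arm test at two-sided 0.05, with 1.06 read as a standardised difference.

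**Step 2: the test as literally named.** If participants were paired arbitrarily across two arms of 15, the noncentrality would stay at 1.06/√2 × √15 = 2.903, but with 14 df and a critical value of 2.145. Power is 0.770. The p-value would depend on the pairing chosen, and the test could not be run on all participants if arm sizes differed.

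**Step 3: baseline-adjusted comparison.** Take 1.06 as standardised on the SD of change, with equal SDs at baseline and follow-up. The change-score variance is proportional to 2(1 − r) and the ANCOVA residual variance to 1 − r². Their ratio (ANCOVA to change score) is (1 − r²)/(2(1 − r)) = (1 + r)/2. The effective d is 1.06/√((1 + r)/2), with 27 df.

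| r (assumed) | Variance ratio | Effective d | Power, 15 per arm |
|---|---|---|---|
| 0.5 | 0.75 | 1.224 | 0.90 |
| 0.6 | 0.80 | 1.185 | 0.88 |
| 0.7 | 0.85 | 1.150 | 0.86 |
| 0.8 | 0.90 | 1.117 | 0.84 |
| 0.9 | 0.95 | 1.088 | 0.82 |

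The comparator is 0.80 for an unadjusted t-test on change. The gain runs from about 10 percentage points at r = 0.5 to about 2 at r = 0.9.

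**The case against.** **Exploratory status.** Safety is the primary outcome and has its own between-arm test. Describing direction and testing only if numbers allow is a common stance for exploratory endpoints in a Phase 1b trial of this size. This stands, and it limits the severity. It does not remove the conflict with a Sample size section that builds the trial on this outcome.

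**Loose wording.** In a three-arm trial the word may have been meant as pairwise (each dose against placebo), or as change from Baseline compared between arms. The unpaired power calculation and the listed between-cohort changes make that likely. If so, the defect is mainly one wrong word. The word still needs correcting, because a literal reading gives a different and ill-defined test, and the comparison would still be optional. Deliberate cross-arm pairing is implausible. Its cost would be about 3 points of power, and arbitrary pairing does not by itself inflate type I error.

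**ANCOVA is a preference.** An unpaired t-test on change is valid under randomisation. That is right: the adjustment is recommended for efficiency, and its gain rests on an assumed correlation.

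**Stronger readings that the article does not support:**

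- That the baseline data are discarded. They are used, through change from Baseline; the only loss is efficiency.
- That the visual check is a rule for declaring benefit. The text says "visually checking the outcome measures moved in the expected direction for each allocation group", which covers the placebo arm too, and it attaches no success criterion. A false-positive rate for that check therefore cannot be derived.
- That the cytokine analysis has the same fault. The immune-status section says "Mean cytokine levels in placebo and hookworm groups will be compared by general linear models", which is a valid between-arm method and can include baseline.
- That drop-out will cut the arms to 12. Recruiting 54 and losing 20% leaves 43.2, or about 14 per arm.

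**Conclusion.** The paragraph is wrong as written and should be fixed. It names a paired test between unpaired groups, makes it optional, and otherwise commits only to within-arm comparison. The 80% power for 15 per arm rests on an unpaired between-arm t-test that the analysis section never names. This is a fault in what is stated, not a detail deferred to an analysis plan.

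The consequence is confined to secondary, exploratory outcomes; the primary safety conclusion does not depend on it. A reader might infer that the trial can yield no valid metabolic comparison. That goes too far: the randomised arms and the baseline and follow-up measurements support one, and the text only has to commit to it.

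The reproduction in Step 1 assumes two-sided 0.05. The power range of about 90% to 82% also assumes that 1.06 is in SDs of change, that SDs are equal at the two times, and that r lies between 0.5 and 0.9.

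**What to change.** In the Metabolic parameters section:

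- Delete the word for paired and the condition on sample size.
- Keep the visual check of direction as description only.
- State the comparison, for example: each metabolic outcome will be compared between each dose group and placebo at 24 months by ANCOVA adjusted for the participant's Baseline value, and reported as an adjusted mean difference with its 95% confidence interval.
- If a categorical metabolic outcome is intended, name an unpaired comparison for it.
- Any before/after summaries within an arm should be labelled descriptive.

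In the Sample size section, say that the calculation refers to an unpaired comparison of two arms, give its alpha and sidedness, and say which SD standardises the 1.06.

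The cost is a few sentences. The Baseline and 24-month values are already scheduled, so no new data, visits or participants are needed. Transformation of HOMA-IR and any repeated-measures model can be left to the analysis plan.

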##### Impact of helminth infection on immune status

Serum samples collected at each scheduled visit will be batch-analysed using a custom-panel of 17 cytokines (IFNγ, IL-1β, IL-12p70, IL-2, IL-4, IL-6, TNF, IL-10, IL-17A, IL-12p40, IL-5, IL-13, IL-15, IL-18, IL-33, MCP-1, MIP-1α) for circulating inflammatory biomarkers associated with metabolic disease using cytometric bead array. Mean cytokine levels in placebo and hookworm groups will be compared by general linear models. Peripheral blood mononuclear cells will be processed at scheduled visits and analysed using flow cytometry for expression of markers of cell phenotype (CD3, CD19, CD4, CD8), activation (CD27, CD45RA, CD45RO, CD69) and function (CD25, CRTH2, CTLA4, FOXP3, IL-2, IL-4, IL-5, IL-10, IL-17A, IFNγ and TNF).

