	Exclusion criteria: Pregnancy, established chronic disease (CVD, diabetes, cancer, renal, gut disorder), history of substance abuse or current substance abuse, major allergies, known immunodeficiency disorder, asthma, taking prescribed medications or nutritional supplements likely to interfere with study outcomes, inability to provide informed consent.
Study type	Interventional
	Allocation: block randomised; intervention model: parallel assignment; Masking: double-blind, sealed envelopes and containers
	Primary purpose: prevention
	Phase 1
Date of first enrolment	March 2018
Target sample size	45
Recruitment status	Recruiting
Primary outcome(s)	Safety of experimental inoculation with 20 L3, defined by (a) Number of reported adverse events (AEs), relative to placebo cohort, (b) Assessment of general health and (c) Successful completion of 24-month trial. Adverse reactions: including but not limited to abdominal pain, rash, fever, weight loss, fatigue, nausea (mild, moderate or severe as assessed by trial doctor).
Key secondary outcome(s)	Changes in insulin sensitivity from blood pathology taken at each participant contact point during the 24-month trial; Change in BMI measured by any alteration in weight (kg) and height (cm); Change in waist circumference (cm) Change in bacterial richness of microbiome measure by shotgun assay of faecal sample

Hypotheses are that experimental infection with the human hookworm *Na*
will be well-tolerated and safe in this cohort of otherwise healthy but obese women and men.will induce a biased Type 2 and regulatory immune response with concomitant suppression of systemic, pro-inflammatory Type 1 responses.will stabilise or improve determinants of metabolic disease.will modify the composition of the gut microbiota.

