The treatment period will last up to 104 weeks during which participants will be required to attend the clinic for two inoculation visits eight weeks apart and four evaluation visits approximately 26 weeks apart. Participants may also have telephone and/or Skype appointments with a designated study team member to monitor their health status and promote retention; these visits will be scheduled with participants by negotiation. At the end of the treatment period, participants will have their final blood and stool tests and DEXA scan, complete the scheduled questionnaires, and undertake an exit consultation and examination with the study doctor. Furthermore, as a mandatory requirement of the study, participants will be provided with the anthelmintic treatment mebendazole (100 mg to be taken twice daily for 3 days to clear the hookworm infection) at no cost to them; however, it is not mandatory for participants to take this medication. Participants electing to refrain from taking the anthelmintic treatment (that is choosing to keep their helminths) following completion of the 104-week period will be advised that their future medical care will be passed onto their general practitioner. At 104 weeks, the study will become unblinded, and there will be an optional 52-week extension to the study for willing participants to examine the impact of de-worming medication on safety, immunological and metabolic parameters.

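### The cytokine analysis compares mean levels between groups without naming the baseline sample or the repeated visits, so it does not match the stated outcome and gives up precision at 15 per arm

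*Protocol article*

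**What the plan says.** The section on the impact of infection on immune status states the measurement, "Serum samples collected at each scheduled visit will be batch-analysed using a custom-panel of 17 cytokines", and then the analysis, "Mean cytokine levels in placebo and hookworm groups will be compared by general linear models". It gives no further inferential detail for the panel. It does not mention a covariate, how visits enter the model, whether the two doses are kept apart, the measurement scale, a significance level or an error-control rule.

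Other sections supply the context:

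- The treatment period has "two inoculation visits eight weeks apart and four evaluation visits approximately 26 weeks apart". The Abstract and the baseline visit section add a blood sample before inoculation.
- The Sample size section sets the arms: "15 to be infected with 20 x L3, 15 to be infected with 40 x L3, and 15 in the placebo control group".
- The Outcomes section lists the immune outcome as secondary and words it as fluctuations in Type 1 and Type 2 responses.
- One of the four hypotheses at the end of the Background is that infection "will induce a biased Type 2 and regulatory immune response with concomitant suppression of systemic, pro-inflammatory Type 1 responses".
- The Aims call the metabolic, immune and microbiological work exploratory.
- For the parallel outcomes the article does bring in baseline or time. The metabolic section compares baseline with follow-up. The microbiota section compares baseline, one year and two years longitudinally.

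**The concern.** The design yields a pre-inoculation value and a series of follow-up values for each participant and cytokine. The outcome is about movement over time. The one stated contrast is a difference in mean level between groups. An analyst who followed that sentence literally would set aside the baseline sample and would have no instruction on combining or separating visits. The neighbouring sections give that direction for their own outcomes, so the gap is specific to the cytokines.

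Precision is what is at stake. With 15 per arm, variation between people that was already present at baseline stays in the error term, and a real immune shift is easier to miss. A second, smaller matter is that 17 results will be read together, and the text does not say whether they are hypothesis-generating or are to be judged against an error rate.

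**Working it through.** **Inputs.** From the article: 15 per arm, three arms, 17 cytokines, four evaluation visits. Assumed, because the article does not give them: two-sided 5% significance, a baseline to follow-up correlation of 0.5 to 0.7, and the correlations among cytokines and among visits used below.

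**1. The plan's own figure.** The article says "A total of 15 participants in each group reflects 80% power to detect an effect size of 1.06 using the T-statistic", having explained that "we have adapted the SUGARSPIN HOMA-IR result [29] and assume an effect size of 1.06 over 2 years". It concerns HOMA-IR, not cytokines, but it shows which significance level is consistent with the plan.

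- Normal approximation: detectable effect = (1.96 + 0.8416) × √(2/15) = 2.8016 × 0.3651 = 1.023, the article's Z figure.
- Noncentral t with 28 degrees of freedom: an effect of 1.06 gives power 0.8001.

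Both figures reproduce at two-sided 5%. That supports the assumption, although the article never states a level.

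**2. What baseline adjustment is worth.** Adjusting for baseline multiplies the residual variance of a follow-up comparison by 1 − ρ², where ρ is the baseline to follow-up correlation.

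| ρ | 1 − ρ² | Variance cut | Equivalent participants per arm | Detectable effect (normal approximation, follow-up SD units) |
|---|---|---|---|---|
| none used | 1.00 | 0% | 15 | 1.023 |
| 0.5 | 0.75 | 25% | 15/0.75 = 20 | 1.023 × √0.75 = 0.89 |
| 0.7 | 0.51 | 49% | 15/0.51 = 29 | 1.023 × √0.51 = 0.73 |

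These rows are for one dose against placebo at one visit and ignore the small cost of estimating the covariate.

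**3. Reading 17 results together.** With one test per cytokine and independence, the chance of at least one false positive is 1 − 0.95^17 = 0.58. Cytokines are likely to be correlated, so this was simulated with no true effect: normal data, 15 per arm, equal correlation among cytokines, placebo against both hookworm arms combined, 4,000 runs. The simulation gives 0.57 under independence, close to the formula.

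| Correlation among cytokines | One test each | Separate tests at 4 visits, within-person correlation 0.5 | Same, within-person correlation 0.8 |
|---|---|---|---|
| 0.3 | 0.51 | 0.91 | 0.82 |
| 0.5 | 0.39 | 0.81 | 0.70 |
| 0.7 | 0.27 | 0.66 | 0.52 |
| 0.8 | 0.22 | 0.56 | 0.42 |

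The four-visit columns use 2,000 runs and apply only if each visit is tested on its own, which the article does not say.

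**The case against.** The strongest reply is that the article is silent and has not decided against anything. A general linear model can carry a baseline covariate and a repeated-measures structure, and nothing in the text rules these out. A condensed article may leave covariates, transformation and multiplicity for a biomarker panel to a full protocol or analysis plan that is not shown. This stands to the extent that the plan cannot be said to have chosen an unadjusted analysis. It does not remove the mismatch between an outcome about fluctuation and a stated contrast of mean levels, in an article that does bring in baseline or time for the parallel outcomes.

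Several stronger readings are tempting, and the documents do not support them:

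- *A false immune finding is more likely than not.* This needs a 5% level, a separate test per cytokine, weak correlation, and any single nominal result being read as an immune effect. None of these is stated. With one test each, the probability is already 0.39 at correlation 0.5.
- *Visits are tested separately, or pooled as if independent.* Neither scheme appears in the text, and they exclude each other, so error rates derived from the two cannot be put side by side as properties of this plan. The visit schedule table is not shown, so the samples entering the analysis cannot be checked.
- *Leaving out baseline inflates the false-positive rate.* In a randomised comparison it does not; it costs precision.
- *Concentrations are analysed on the raw scale.* Speaking of mean levels does not exclude transformation.

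The Aims label the immune work exploratory, and the hypothesis is a directional pattern across Type 1 and Type 2 markers. The chance of any one of 17 results crossing 5% is therefore only a rough measure of the risk of wrongly supporting it. This stands, and it is why the multiplicity part is a light addition.

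**Conclusion.** The point holds as one of precision and of fit between outcome and analysis. As worded, the cytokine comparison does not draw on the baseline sample or address change over time, although the data for both are to be collected. On an assumed baseline to follow-up correlation of 0.5 to 0.7, adjustment cuts variance by about 25% to 49%; a lower correlation would give less.

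The multiplicity part is secondary. At an assumed two-sided 5% with one test per cytokine, the chance of at least one false positive is about 58% under independence and about 27% at correlation 0.7; it is higher if visits are tested separately. A reader might infer that the immune results will probably mislead. That does not follow from the text. The supportable conclusion is that the results need either an exploratory label or a stated error-control rule. The primary safety outcome is not affected.

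**What to change.** Replace the analysis sentence with wording such as this: each cytokine, log-transformed if skewed, will be analysed by a linear mixed model with baseline value, arm (placebo, 20 L3, 40 L3), visit, arm-by-visit interaction and a participant random effect, and each dose will be reported against placebo with a 95% confidence interval. Add one sentence saying either that the 17 cytokine results are exploratory, or that they are adjusted for the false discovery rate at one named time point with other visits descriptive.

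Baseline is better entered as a covariate than subtracted. A change score has variance 2(1 − ρ) relative to an unadjusted follow-up value, which is 1.00 at ρ = 0.5 and 0.60 at ρ = 0.7, against 0.75 and 0.51 for the covariate.

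The change uses samples already planned and places nothing further on participants. The cost is slightly more analysis work and, if the false discovery rate is controlled, fewer nominally significant cytokines.

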##### Impact of helminth infection on faecal microbiota

Faecal specimens collected in anaerobic sample collection containers will be stored at − 80 °C and, later, DNA will be extracted prior to genome-wide shotgun sequencing to describe the composition and metabolic potential of the microbiota. Following quality filtering, the QIIME pipeline will be used for operational taxonomic unit (OTU) analysis and Beta diversity will be analysed using UniFrac. Longitudinal comparisons will be made between Baseline, 12 and 24 months looking at diversity and any changes in OTUs between treatment and placebo groups. These data, along with clinical and immunological data, will be analysed subsequently in an integrative fashion to more comprehensively define the biological impact of experimental *Na* infection on individuals with metabolic disease.

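### The faecal microbiome plan pairs a shotgun assay with an OTU/UniFrac workflow made for marker-gene amplicons, names no analysis for metabolic potential, and does not carry the registered richness outcome into the Outcomes or analysis text

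*Protocol article*

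**What the plan says.** Three places in the protocol article bear on this.

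- **Table 1, key secondary outcomes**, registers "Change in bacterial richness of microbiome measure by shotgun assay of faecal sample". It is one of four entries; the others are insulin sensitivity, BMI and waist circumference.
- **Outcomes** gives the microbiome outcome as longitudinal and between-group change in faecal microbiome composition. Richness is not mentioned.
- **Impact of helminth infection on faecal microbiota** fixes the assay: "DNA will be extracted prior to genome-wide shotgun sequencing to describe the composition and metabolic potential of the microbiota". The next sentence fixes the analysis: "Following quality filtering, the QIIME pipeline will be used for operational taxonomic unit (OTU) analysis and Beta diversity will be analysed using UniFrac". The comparisons follow: "Longitudinal comparisons will be made between Baseline, 12 and 24 months looking at diversity and any changes in OTUs between treatment and placebo groups". The results are then to be combined with the clinical and immunological data in an integrative analysis.

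The last of the four hypotheses at the end of the Background is that infection will change the composition of the gut microbiota.

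**The concern.** The assay and the named analysis belong to different types of experiment. An OTU is conventionally a cluster of reads from one amplified marker gene, and UniFrac needs a phylogenetic tree on which those units sit. Shotgun reads come from positions all over the genome, so they do not cluster directly into OTUs. The reason for choosing shotgun sequencing over an amplicon assay is the added functional information, and the named workflow does not use it.

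The microbiome outcome is also described in different terms in Table 1 and in the two later sections. If the registered measure is not named where outcomes and analyses are defined, the choice of richness index, taxonomic level and read depth stays open until the data are in hand. For a trial whose stated rationale includes mechanisms acting through the microbiota, that weakens what can be claimed from this part of the study.

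**Working it through.** No arithmetic applies. The plan gives no figure on this point, and no power or sample-size number depends on it. The check sets the statements side by side. What OTU clustering and UniFrac require is general methods knowledge, not something the article states.

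**1. Assay against workflow.** Input: genome-wide shotgun reads. Only preparatory step named after sequencing: quality filtering. Next step: OTU analysis in QIIME and UniFrac. To get from the first to the last, marker-gene reads would have to be extracted and matched to a reference OTU set and tree, or reads profiled against reference genomes that have a phylogeny. Neither is stated. Under the first route, all reads outside the marker gene go unused for taxonomy.

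**2. Purpose against output.** The assay has two stated purposes.

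| Stated purpose | Named analysis that could deliver it |
|---|---|
| Composition | OTU table and UniFrac beta diversity, once the missing step is supplied |
| Metabolic potential | None: the listed comparisons are of diversity and OTUs, and neither gives gene or pathway content |

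The later integrative analysis takes these data as its input, so it does not supply the missing functional read-out.

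**3. Registered outcome against analysis.**

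| Place | Microbiome measure |
|---|---|
| Table 1 | Change in bacterial richness |
| Outcomes | Change in composition |
| Analysis section | OTU changes, unspecified diversity, and UniFrac as the one specific metric |

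Richness is a within-sample count. UniFrac is a distance between samples, so it cannot itself give a change in richness. An OTU table can, by counting the units observed in each sample, and the general word diversity may be meant to cover this. Richness is therefore derivable but not specified.

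**4. Extent.** One of four hypotheses and one of four registered key secondary outcomes are touched. The Aims call the microbiological work exploratory. The primary outcome is safety, and the sample-size section rests on HOMA-IR.

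**The case against.** The strongest reply is that nothing here is impossible. Marker-gene reads can be pulled from shotgun data and placed on a reference tree, UniFrac can be run on a reference-genome phylogeny, and richness can be counted from the resulting table. A journal article may also leave read extraction, reference databases, read depth and functional tools to the full protocol or analysis plan. This reply largely stands, and it sets the limits of the point. A reader might infer that the microbiome parameters cannot be derived as written; the text does not support that.

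A reader might also infer that uneven sequencing depth between batches or visits would show up as a treatment effect. That does not follow. A shift in depth between visits would affect all three randomised groups, and a spurious group difference would need depth to differ by group. Nothing in the article suggests this, and the data analysts are blinded. Nor does the article give any figure for the share of reads that fall on a marker gene, so the loss under the literal reading cannot be sized from it.

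The reply does not dispose of the mismatch itself. The article is not silent: it names a pipeline, a unit, a metric and the comparisons, and these do not fit the assay named in the sentence before. The difference between Table 1 and the later sections is likewise a difference between statements, not just a condensed description.

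**Conclusion.** The point holds as a mismatch and a gap in specification, not as an analysis that cannot be done. The named OTU/UniFrac workflow is not the natural one for the stated shotgun assay, no named analysis yields metabolic potential, and the registered richness outcome is not named in the Outcomes or analysis sections. The first part rests on the conventional meaning of OTU and UniFrac. The other two can be read directly from the text.

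The size is modest: an exploratory secondary outcome, with no effect on the primary safety outcome or the sample size. It is worth correcting because a better-fitting method is available from the same samples and the same sequencing.

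**What to change.** Replace the OTU sentence with wording along these lines:

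> Quality- and host-filtered shotgun reads will be profiled taxonomically against a reference-genome database, and gene and pathway abundance will be profiled to describe metabolic potential. The registered microbiome outcome is change from Baseline in species richness at a common read depth, compared between each hookworm group and placebo at 12 and 24 months. Between-sample composition will be compared using one prespecified distance, UniFrac on the reference phylogeny.

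UniFrac is given as an example that keeps the current choice; another single distance would serve if fixed in advance. The following sentence should refer to taxa instead of OTUs.

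Then make Table 1, Outcomes and the analysis section agree: name richness in Outcomes as the registered measure, with composition listed beside it as a further measure, since the hypothesis is framed in terms of composition.

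The cost is wording only; samples and sequencing do not change. The downside is that bringing samples to a common read depth discards some reads. It is still reasonable here, because observed richness rises with depth and uneven depth would add noise to the change from Baseline.
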